### **Qualitative Methods: Credibility & Trustworthiness**

Creswell (2009) states that themes that are established by converging multiple perspectives from participants can claim to possess added validity. And in addition, as has already been highlighted as part of the mixed methods approach in this study, the qualitative data will be triangulated with the quantitative data. The approach of "validating" qualitative data largely depends on the approach of the researcher; Silverman (2006) states that those who adopt a "realist" approach to qualitative data, come from a positivist or emotionalist standpoint, and treat respondents' answers as describing some external reality (such as facts or events) or internal experience (such as feelings or meanings). If a researcher follows this approach, it is appropriate to incorporate various strategies into the research design to ensure the accuracy of the researcher's interpretation, although he stops short of using the term "validity". Silverman (2006, 2010) suggests such measures might include checking the accuracy of what respondents say in interview by other observations (i.e. does what they say match with what they do), or using measures such as inter-coder agreement and computer-assisted qualitative data programs as a means of securing a "fit" between your interpretations and some external reality.

An alternative approach is to treat interview data as actively constructed 'narratives' involving activities which themselves demand analysis (Silverman, 2010) or accessing various stories or narratives through which people describe their world (Riessman, 2008; Gubrium and Holstein, 2009). This approach is from a constructionist standpoint, where interviewers and interviewees are always actively engaged in constructing meaning (Silverman, 2006). Rather than be concerned with accurate depictions of 'facts' or 'experiences', the researcher takes as their topic how meaning is mutually constructed (Atkinson and Coffey, 2002).

So which of these two strikingly different approaches to conceptualizing this research problem – and, in turn, leading to contrasting ways of looking at interview data – is preferable? Silverman (2006) points out that neither approach is without its problems: realist approaches may de-emphasize the multiple meanings that people attach to what they do, while the constructionist approach to defining a research topic can overcome that problem but may be criticized for losing sight of important substantive issues. The research questions under scrutiny here wish to explore participants' thoughts and feelings regarding their own professional development in general, and their mentoring experience in particular, placing it in an "emotionalist" category; but can the criticism of missing multiple meanings as people speak with "multiple voices" be addressed? Silverman suggests technical solutions to this problem can be asking the same question in several different ways or comparing what respondents say with what they do.

In view of the above, it is my intention to triangulate the different data sources of information (by examining evidence from interviews with participants, interviews with mentors, and observations of the mentoring process) in order to justify themes in a coherent and appropriate manner, to enhance the accuracy of what respondents say in interview by making observations of them during the mentoring process, and to address the fact that participants may attach multiple meanings to what they do. The interview questions will also ask questions about the mentoring process in different ways, to address this latter concern.

Other measures employed to combine insight with rigour in qualitative accounts include an open and honest narrative that clarifies the bias the researcher brings to the study; self-reflection about how the interpretation of the findings is shaped by the researcher's background is a feature of good qualitative research and resonates well with audiences (Creswell, 2009). Openness and honesty should also include the presentation and discussion of information that is contrary to the themes that have been developed; this adds to the realism, credibility, and therefore the validity of an account because clinical experience involves different perspectives that do not always harmonize neatly. While most evidence will build a consensus for a theme, information that contradicts the general perspective of the theme will also be included and discussed. Finally, as well as my background introducing potential bias, it also adds validity. Creswell (2009) states that the greater the experience that a researcher has with participants in their actual setting, the greater the validity of the findings. As a physiotherapist who has spent prolonged time in the field of musculo-skeletal outpatient physiotherapy, and worked in the University Health Board, I am able to provide detail about the people and the clinical context. Also, having undertaken and delivered Masters level mentoring programmes to facilitate clinical reasoning I have developed an in-depth understanding of the phenomenon under study. In short, this experience should lend credibility to the narrative account.

Finally, measures to improve consistency and reliability will also be employed (Gibbs, 2007). In the case of this study, transcripts of interviews will be checked to ensure that errors are not made during transcription. Also, as has already been discussed, a codebook will be used to ensure that definitions and meanings of codes do not drift during the coding process. Also, as a single researcher, a second person will be enlisted to cross-check my codes in order to establish whether similar codes would be attributed to sections of the interview text. Miles and Huberman (1994) recommend a minimum of 80% inter-coder agreement for good qualitative reliability; this can be established using the nVIVO qualitative computer software package.

## **Economic Evaluation**

### **Rationale for Economic Evaluation**

The intervention in this situation is educational, and one of the primary issues with any educational input is cost (McMeeken 2008). Indeed, the implications of training costs has been considered at government level, and was one of the key factors in the rationale for the set up of the National Health Service University (NHSU), in order to provide its own training and so reduce expenditure to higher education institutions used by the NHS to train and develop its staff (Flood, 2003). Ironically, the NHSU failed to get off the ground and the nascent institution was abolished in 2005 at an alleged loss of at least £72 million (Flood, 2005, Harding, 2005, Scott, 2004, Taylor et al., 2007). The consideration of cost of training is evident throughout the healthcare literature (Currie et al, 1997; Hlusko et al, 1998, Flood, 2003, Carlisle 2009, Kalet, 2010) and studies examining the efficacy of training programmes have begun to include economic evaluation components (Akkers et al, 2006; Goodwin et al, 2001; Lundberg et al, 2010; Wingard et al, 2004). Any improvements in other outcomes need to be measured against costs of intervention (Jette and Latham 2010).

### **Aim of Economic Evaluation**

The aim of the economic evaluation is to assess the costs associated with the training of physiotherapy staff from the perspective of the UK NHS and to utilise measures of effect alongside the costs to determine the extent to which it can be regarded as an efficient use of NHS funds.

### **Design of Economic Evaluation**

The economic evaluation will provide a comparative analysis of the alternative training programmes available to participants (usual training only verses the clinical reasoning intervention plus access to usual service provision). A cost-consequences analysis will provide a clear descriptive summary of the costs (cost of the intervention programme / cost of the alternative programme – no clinical reasoning intervention) and the consequences (outcomes for the participants / service utilization/utility gains). Costs and consequences will be reported separately enabling a full evaluation of the different outcome components (changes in function/HRQL/activation/resource utilization/utility gains) and related to the costs for each of the alternative courses of action. This information is useful to policy makers in determining whether the intervention is 'worth it' in relation to its generalisability. Further, distinction will be made between the costs incurred and outcomes generated in each programme area, so as to assess variation and potential for efficiency gains. Further, a series of sensitivity analyses will be undertaken to assess implications of parameter variation and a threshold analysis used to determine extent to which costs and outcomes need to vary to alter conclusions relating to relative cost-effectiveness of programme.

### **Economic Evaluation Methods**

Costs will be categorised according to whether they are research or programme specific and care will be taken with regard to the attribution factors used to determine costs of intervention programme.

Further, the agencies that incur costs will be clearly specified, as will the agencies that benefit from reductions in resource utilisation, so as to enable inter-sectoral comparisons to be undertaken. Programme outcomes will be utilised within the economic evaluation in conjunction with the costs to inform the cost consequences analysis and to determine the extent to which the programme can be regarded as representing value for money.

All inputs and services provided – from all agencies and families participating - will be documented in descriptive terms and wherever possible translated into monetary terms using appropriate published unit cost data (e.g. BNF, PSSRU, NHS Reference Costs).

A series of cost modules will be developed, to establish a profile of costs and establish the agency that incurred the costs, as outlined in table 6 below.

| Table 6: Cost modules   |                                                                                      |                                                                                                                                                                                               |                                                                                                                           |
|--------------------------------|--------------------------------------------------------------------------------------|-----------------------------------------------------------------------------------------------------------------------------------------------------------------------------------------------|---------------------------------------------------------------------------------------------------------------------------|
| Type:                   | Aspects:                                                                      | Specifics:                                                                                                                                                                             | Collected By:                                                                                                      |
| Research & Evaluation Specific | Questionnaire Design and Production

Data Collection, Processing & Management  | Printing Costs

Down time for mentors / participants from patient care for interviews, assessment of therapist performance                                                              | Lead Researcher                                                                                                           |
| Training Programme Specific    | Direct Programme Costs (i.e. costs associated with the training of physiotherapists) | Down time from patient contact by mentor / trainer to deliver training

Down time from patient contact by participant to receive training

Equipment required to deliver training | Monthly Training Requirements Form (Appendix E)                                                                           |
|                                | Indirect Programme Costs                                                             | Costs of participation, transport for participants or mentors (if / where applicable)                                                                                                         | Monthly Training Requirements Form (Appendix E)                                                                           |
| Service Utilisation Costs      | Costs of physiotherapy intervention                                                  | Number, length and type (individual /group) of attendances                                                                                                                                    | Physiotherapy records / D&T system                                                                                        |
|                                | Costs associated with the uptake of traditional health/social care services          | e.g. GP, hospital visits; referral to secondary care for opinion or intervention, or for diagnostic imaging; use of prescription medication                                                   | Baseline, Discharge and 12 month follow up questionnaires (Appendix A)

Finance Department, University Health Board |

#### **Costs of usual training and clinical reasoning programmes**

Overall costs of providing the training programmes will be computed and include the costs of implementing and delivering the programmes and any costs incurred by participants (e.g. Transport to another site to receive training). The overall cost per participant will be computed, for the overall study and for each site. However, a clear demarcation will be made between set up costs, implementation costs and those that would occur if the programmes were to become part of subsequent mainstream provision.

The costs of implementing and delivering the programmes will include staff time, venue and equipment costs, provision of support facilities, materials utilised etc.

As mentors and trainers are supplied from within the physiotherapy service, the staffing costs associated will be readily available. Therefore the actual salary costs of mentors will be obtained and then multiplied by the hours of non-patient contact time as part of the mentoring to derive the average staffing costs for facilitators. The non-patient contact time of mentees will also be calculated in the same way. The Monthly Training Requirements Form (Appendix F) will be entered into an Excel database, which will be forwarded to the lead researcher for analysis with assistance from the research supervisor. This would generate the information necessary for computing the cost associated with providing each mentoring programme.

### **Service utilisation**

Participation by physiotherapists in the training programmes is likely to result in changes in the outcomes of patients being treated by those physiotherapists, including their utilisation of physiotherapy services, and utilisation of other services provided by a range of agencies. These need to be captured within the trial so as to identify the extent of costs offset as a result of the training programmes, and which represent one aspect of the outcomes generated by the programmes. This will be achieved via section B of data collection questionnaires during the study period, to establish service utilisation of patients at baseline and changes on discharge from treatment and over time (long term follow up at 12 months).

The combination of changes in service utilisation over time and costs of programme delivery will result in a net cost per participating physiotherapist, which will be used in the assessment of the relative cost-effectiveness of the programmes. The extent to which these changes in service utilisation are sustained over time inform mentors, staff and key stakeholders in order to assess the longer term efficiency of the programmes.

Analysis will be conducted within the context of representing the data at 'that point in time'. No variables from the main database will be changed, but variables representing costs will be added for the specific purpose of the economic evaluation only. Therefore as the project continues, a second analysis of the service utilisation data will be conducted using the baseline and discharge follow up data as it stands at 'that point in time', capturing any changes made to the data, and a second interim report with accompanying SPSS/Excel file will be produced. A third and final analysis at 12 months will use the data representing the baseline, discharge and the 12 month follow up data points as they stand at 'that point in time' - the final report with accompanying SPSS/Excel file will form part of the PhD thesis. Cost data may also change over the time periods and will be updated when necessary. For the final analysis changes in resources utilised over time will be calculated and used in conjunction with the costs of delivering the programmes to generate the overall cost of programme delivery.

### **Outcomes**

The changes in primary and secondary outcomes will represent the consequences of the delivery of training programmes to be used in conducting the cost consequences analysis. As part of this process the responses to EQ5D at various time-points will be used to generate utilities to derive QALYs gained as a result of the programmes and compute the cost/QALY ratio.

### **Data analysis**

The cost consequences analysis will be conducted from the perspectives of the UK NHS to determine the extent to which the programme can be considered to represent value for money. The cost consequences will

be assessed at the end of the trial and post-trial modelling will be employed to assess the cost consequences for over longer time horizons than possible with the study period.

Changes in resources utilised (4.2) over time will be calculated and used in conjunction with the costs of delivering the programme (4.1) to generate the overall cost of programme delivery per participant and per patient, which will represent the incremental cost of providing clinical reasoning training relative to usual training provision

The changes in primary and secondary outcomes - (including changes in utility scores derived from the EQ5D responses at baseline and 1 year follow-up) will be used alongside the net cost of training programme delivery in the cost consequences analysis to generate a set of indicators of relative cost-effectiveness within the study period, based on incremental cost and incremental outcomes.

Missing data will be dealt with by employing an appropriate imputation-based method for effectiveness and quality of life data (Brazier et al., 2007) while the usual method for dealing with censored data relating to costs will be to employ the weighted cost method with known cost histories (Young, 2005).

Future costs and benefits will be discounted at the prevailing rate (currently 3.5%pa) to bring into present values. Costs and benefits will be discounted at 0% and 6% in the sensitivity analysis.

A series of one-way sensitivity analyses will be undertaken to assess the extent to which changes in the variables employed affect the baseline estimates. The variables will be adjusted in line with emerging distributions of data values and impact on baseline estimates computed. A threshold analysis will also be undertaken to determine the degree of parameter variation required to alter conclusions derived from baseline findings.

A series of scenarios will be developed and utilised within an economic model to assess the relative efficiency of clinical reasoning training over longer time horizons

Probabilistic sensitivity analysis will be undertaken to ascertain cost-effectiveness acceptability curves produced to assess the probability that clinical reasoning training represents value for money

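### As written, the incremental cost of mentoring is a before-and-after sum that does not subtract the change seen under usual training

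*Protocol*

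**What the plan says.** The Design of Economic Evaluation section sets out a comparison: "The economic evaluation will provide a comparative analysis of the alternative training programmes available to participants", namely "usual training only verses the clinical reasoning intervention plus access to usual service provision".

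The sections that turn this into a quantity read differently. Service utilisation says the questionnaires are used "to establish service utilisation of patients at baseline and changes on discharge from treatment and over time (long term follow up at 12 months", in order to "identify the extent of costs offset as a result of the training programmes". It then states: "The combination of changes in service utilisation over time and costs of programme delivery will result in a net cost per participating physiotherapist". Data analysis repeats the construction: "Changes in resources utilised (4.2) over time will be calculated and used in conjunction with the costs of delivering the programme (4.1". The resulting overall cost is reported "per participant and per patient, which will represent the incremental cost of providing clinical reasoning training relative to usual training provision".

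The Outcomes section treats the effect side alike. Changes in the primary and secondary outcomes are taken as the consequences of delivering the training, and Data analysis uses utility change from baseline to one year.

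On calendar time, the clinical sections (Statistical methods, and Challenges in using this design) recognise that time can be confounded with the intervention and put time effects in the model. The economic section neither repeats this nor refers to it.

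**The concern.** A change from baseline to discharge and 12 months in patients of mentored physiotherapists contains two things: whatever would have happened under usual training, and whatever mentoring added. Only the second is incremental. The written rule adds the whole change to the programme cost and calls the sum incremental.

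The quantity matters because it feeds the cost-effectiveness indicators, the cost/QALY ratio, the threshold analysis and the acceptability curves, and value for money to the NHS is the stated aim of this component. If the rule is followed to the letter, those outputs rest on a before-and-after figure and not on the randomised comparison. Repairing it by a simple subtraction of control from mentored patients brings in a second problem, because in a stepped wedge the mentored patients are seen later.

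**Working it through.** **Layout.** The protocol states no economic figure to reproduce, so the layout was checked against its power calculation. Inputs: 12 physiotherapists, 3 clusters and 4 time points (Power calculation summary), 4 physiotherapists per cluster (Table 5), 12-month periods (Challenges section). With clusters crossing at steps 2, 3 and 4:

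- U = 4×3 + 4×2 + 4×1 = 24
- W = 4² + 8² + 12² = 224
- V = 4×3² + 4×2² + 4×1² = 56

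These match Appendix E. With N = 9, σ² = 4/9 and τ² = 1, they return its variance of 0.12579, delta of 2.8196 and power of 0.805.

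**The written rule against the promised contrast.** Per patient, let C be the extra programme cost, D the mean change in service cost under usual training (negative for a fall), and E the further change caused by mentoring.

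- Rule as written: C + (D + E)
- Mentored minus usual training: C + (D + E) − D = C + E
- Error of the written rule: D

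The documents give no value for D, so the values below are assumed, with C = 100 and E = 0:

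| D | Rule as written | Control-subtracted |
|---|---|---|
| −200 | −100 | 100 |
| −100 | 0 | 100 |
| −50 | 50 | 100 |
| 0 | 100 | 100 |
| +50 | 150 | 100 |

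The same algebra applies to the utility and outcome changes.

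**Calendar time.** Counting cluster-by-step cells:

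- Control: (3×1 + 2×2 + 1×3)/6 = 10/6 = 1.67
- Mentored: (1×2 + 2×3 + 3×4)/6 = 20/6 = 3.33
- Gap: 1.67 steps, or 20 months

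An unadjusted contrast is therefore biased by 1.67 times the drift per step. An assumed drift of ±10 to ±20 per step gives ±16.7 to ±33.3.

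**Both together.** Assume no mentoring effect, C = 100, and a service-cost change of −100, −80, −60 and −40 at steps 1 to 4 in both conditions.

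- Mentored mean: (1×−80 + 2×−60 + 3×−40)/6 = −53.3
- Control mean: (3×−100 + 2×−80 + 1×−60)/6 = −86.7
- Rule as written: 100 − 53.3 = 46.7
- Unadjusted contrast: 100 + (−53.3 + 86.7) = 133.3
- Least squares with step and physiotherapist terms: intervention coefficient 0, so 100, the correct value

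**The case against.** The best reply is that a comparator is plainly intended. The design section names both conditions, a separate section costs both training programmes, the Data analysis sentence itself ends by referring to usual training, and the next paragraph speaks of incremental cost and incremental outcomes. On that reading, change in resource use is an input for each programme and the increment is the difference between them. This stands as evidence of intent, so a reader should not infer that the plan has no comparator or that the control change will certainly be left out. It does not repair the rule: costing both programmes supplies the training-cost difference, but no sentence takes the corresponding difference in service use.

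A reader might also infer that ordinary recovery will be booked as a saving from mentoring. The documents do not support a direction. Table 6 counts physiotherapy attendances as service costs, and these accrue after baseline, so the change could be a rise.

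Nor does "Cost data may also change over the time periods and will be updated when necessary" show that later patients will be priced at later prices. It follows a description of successive reports, each using data as they stand, and can mean refreshed unit costs for each report.

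Finally, the absence of a step term in a cost model could be left to an analysis plan that is not shown. Alone it would not be a finding. It is included here because the definition has to be rewritten anyway, and the obvious rewrite would be confounded with time.

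**Conclusion.** The point holds as a defect of definition. The rule in Service utilisation and Data analysis, and its counterpart in Outcomes, does not produce the comparison that the design section promises. Taken literally, the error equals the entire change under usual training, of unknown size and sign; the monetary values in the check are illustrations only. If the control change is subtracted without a time term, the remaining bias is 1.67 times the drift per 12-month step, which follows from the layout and assumes roughly linear drift and equal cell sizes.

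The primary PSFS analysis is untouched, and costs and consequences are also to be reported separately, so this affects the value-for-money conclusion only. That conclusion is a stated aim, so the definition should be corrected.

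**What to change.** In Service utilisation, Outcomes and Data analysis, state:

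- Incremental cost per patient is the step-adjusted difference in service cost between mentored and usual-training periods, from a model with step effects and a physiotherapist random intercept, plus mentoring cost minus usual-training cost per patient.
- Incremental outcomes and QALYs are estimated in the same way.
- Within-patient changes from baseline are reported by training condition, as description only.
- All resource use within a given report is valued at one price year.

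The cost is a rewording of these paragraphs and one further regression on data already planned for collection. The interval for the incremental cost will be wider and may be less favourable to mentoring.
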